#### Strategies to improve adherence to interventions {11c}

The main challenge to adherence will be accurate implementation of fluid restriction (or lack thereof) from both a staff and patient perspective. Ward staff including doctors and nurses will be educated about the purpose and implementation of the study. Clear visual communication boards will be present at each participant’s bedside, updated daily with their fluid intake ‘prescription’, which will also be documented in the patient’s medical record. Patients will be educated about their requirements in adhering to a fluid restriction (or not) and will be encouraged to assist in recording and monitoring their fluid intake and output, which will be documented by nursing staff in the electronic patient record as per usual care practices. Any adherence challenges beyond this are expected to reflect the real-world difficulty of implementing a strict fluid restriction.

#### Relevant concomitant care permitted or prohibited during the trial {11d}

Fluid restriction will not be allowed for participants in the tolvaptan group on days that they receive tolvaptan. Tolvaptan will not be allowed for participants in the fluid restriction arm. Otherwise, management decisions will be the responsibility of the treating team. This includes the use of other treatments for hyponatraemia including diuretics, oral solute, or intravenous saline. The treating medical team will retain the authority to withdraw a participant from the trial for any reason.

In the event that a patient becomes significantly hypovolaemic (as demonstrated by development of hypotension or serial urine sodium newly < 20 mmol/L), the patient will not receive either tolvaptan or fluid restriction and may be prescribed intravenous normal 0.9% saline at the discretion of the treating team.

#### Provisions for post-trial care {30}

After completion of the 72-h trial period, patients will revert to usual care. The endocrinology unit is available at all hours on a consult basis to assist other medical teams with the management of inpatients with hyponatraemia before, during, or after the study. Patients will be contacted by phone 30 days after discharge to complete an exit questionnaire and obtain serum sodium result 30 days post discharge.

### Outcomes {12}

Primary and secondary endpoints are shown in Table 3.

**Table 3 Tab3:** Outcomes

**Primary endpoint**	• Change in serum sodium concentrations over time, from day 1 to day 4
**Secondary endpoints**	• Difference between groups of area under the curve of serial direct serum sodium measurements in mmol/L • Serum sodium increment in the first 24 and 48 h • Proportion of patients normalising serum sodium (defined as serum sodium ≥ 135 mmol/L) • Length of hospital stay • Requirement for serum sodium re-lowering with enteral or IV dextrose/water and/or desmopressin o *Main safety outcome: difference between rates of above-target correction of serum sodium leading to attenuation/reversal therapy (e.g. IV dextrose administration)* • Cognitive and functional measures at 24, 48 and 72 h (or discharge if sooner) o Confusion Assessment Method Shortform (CAM-S) score o Hyponatraemia symptom questionnaire score o Timed Up and Go test score • 30-day readmission rate • Exit questionnaire treatment satisfaction score • Serum sodium concentration 30 days after discharge

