## Abstract

**Background:**

Current hyponatraemia guidelines are divided on the use of tolvaptan in hospitalised patients with moderate to severe hyponatraemia, due to an uncertain risk-benefit ratio. We will conduct a randomised trial to test the hypothesis that early use of tolvaptan improves the rate of serum sodium correction and clinical outcomes compared with current standard first-line therapy, restriction of fluid intake, without increasing the risk of serum sodium overcorrection.

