#### Criteria for discontinuing or modifying allocated interventions {11b}

Overcorrection will be defined according to the European guidelines as an increment in plasma sodium of > 10 mmol/L in 24 h [7]. Overcorrection will be defined as a serious adverse event (SAE) and will prompt individualised management by the treating medical team in collaboration with the endocrinology consult service for decisions regarding re-lowering of plasma sodium with intravenous 5% dextrose therapy.

If the serum sodium rise has not exceeded 10 mmol/L in 24 h but is rising at a faster than desired rate, prophylactic intravenous 5% dextrose will be administered, per protocol. In the event that sodium concentration rises by > 6 mmol/L within 6 h of tolvaptan, or > 8 mmol/L within 12 h of tolvaptan administration, this will be initiated at a rate to match urine output, with increased frequency of sodium monitoring (Table 2) in accordance with safety advice issued by Otsuka Australia Pharmaceutical [28]. This infusion will be discontinued if the plasma sodium then falls back within the target range, and serial sodium monitoring will continue as standard protocol.

**Table 2 Tab2:** Thresholds for intervention with intravenous dextrose 5% in the context of sodium rise following tolvaptan dose

Rise in serum sodium	Time post-tolvaptan	Action
> 6 mmol/L	Within 6 h	Commence IV dextrose 5% at rate equivalent to urine output, continue to monitor frequently and cease when sodium back within target range
> 8 mmol/L	Within 12 h	
> 10 mmol/L	Within 24 h	Aim for re-lowering with bolus hypotonic fluid

In the event that daily bloods are not available for any reason, management will revert to a 1.5-L fluid restriction for both groups while awaiting further results.

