##### Biochemistry

Sodium measurements will be performed with simultaneous indirect urea, electrolytes and creatinine and direct measurement with venous blood gas will monitor serum sodium. In patients with serum sodium below 125 mmol/L and all patients following tolvaptan administration, bloods will be performed every 6–8 h in accordance with recommendations [7, 28]. Patient with serum sodium above 125 mmol/L being managed with a fluid restriction (not tolvaptan) will have bloods every 12 h. In the event of discrepancy between these readings, the direct sodium measurement will be preferred due to increased accuracy and faster turnaround time [33]. Daily serum osmolality will be recorded. A daily urine sample at 0600 will monitor urine sodium, osmolality and specific gravity. Daily monitoring of liver function will be performed in tolvaptan recipients for safety given the small risk of liver damage identified in longer-term trials of high-dose tolvaptan used for other indications [23].

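### The main safety outcome counts a fast sodium rise only if it is treated, and the numerical early treatment thresholds apply only after tolvaptan; the arm-neutral overcorrection rate should be listed beside it

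*Protocol article*

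**What the plan says.** The Abstract (Background) hypothesises that tolvaptan improves correction "without increasing the risk of serum sodium overcorrection". Objectives {7} puts the safety hypothesis more broadly, as no increase in adverse events.

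Section {11b} defines the event without reference to arm: "Overcorrection will be defined according to the European guidelines as an increment in plasma sodium of > 10 mmol/L in 24 h". It continues: "Overcorrection will be defined as a serious adverse event (SAE) and will prompt individualised management by the treating medical team". Re-lowering after such a rise is thus open to both arms, at clinicians' discretion.

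Table 3 (Outcomes {12}) does not list the rate of that event. It lists "Requirement for serum sodium re-lowering with enteral or IV dextrose/water and/or desmopressin" and, under it, names as the main safety outcome the "difference between rates of above-target correction of serum sodium leading to attenuation/reversal therapy (e.g. IV dextrose administration".

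The numerical early thresholds in {11b} are a rise of "> 6 mmol/L within 6 h of tolvaptan, or > 8 mmol/L within 12 h of tolvaptan administration". Table 2 is titled "Thresholds for intervention with intravenous dextrose 5% in the context of sodium rise following tolvaptan dose". No matching table exists for fluid restriction.

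The Biochemistry section sets sampling every 6–8 h after tolvaptan and for anyone below 125 mmol/L. For the rest: "Patient with serum sodium above 125 mmol/L being managed with a fluid restriction (not tolvaptan) will have bloods every 12 h". Section {17a} states that the trial is open-label.

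**The concern.** An event enters the main safety outcome only if sodium rises too fast and someone treats it. The second condition works differently in the two arms. Take a rise of 7 mmol/L at 6 h. After tolvaptan it crosses a written threshold, dextrose follows under the protocol, and an outcome event is counted. In a fluid-restriction participant above 125 mmol/L there may be no 6 h sample, and no numerical early rule applies if there is one. Whether that participant is treated depends on clinicians who know the allocation.

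The trial aims to inform guidelines that are divided over exactly this risk. If the headline safety difference partly reflects the rescue rules, an excess on tolvaptan could be read as excess overcorrection when some of it is protocol-mandated prophylaxis.

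**Working it through.** **Plan's own figure.** None exists to reproduce: the document gives no power, precision or margin for the safety outcome. I take 83 per group from Table 5 as given.

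**Step 1. The rules by arm.**

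| Element | Tolvaptan | Fluid restriction |
|---|---|---|
| Numerical early dextrose thresholds | > 6 mmol/L in 6 h; > 8 mmol/L in 12 h | none stated |
| Rise > 10 mmol/L in 24 h | SAE; individualised decision; also a Table 2 row | SAE; individualised decision |
| Sampling, sodium above 125 mmol/L | every 6–8 h | every 12 h |
| Sampling, sodium below 125 mmol/L | every 6–8 h | every 6–8 h |

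The asymmetry lies in the first row and in part of the sampling.

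**Step 2. Gap with identical sodium courses (simulation, 400,000 per scenario).** Assumed inputs, none from the document: 24-h rise Normal with mean 4–6 and SD 3–4 mmol/L; measurement noise SD 0.7–1.0 at baseline and follow-up; either a front-loaded rise (50% by 6 h, 80% by 12 h) or a linear one. Tolvaptan event: > 6 at 6 h, > 8 at 12 h, or > 10 at 18 or 24 h. Fluid-restriction event: > 10 at 12 or 24 h, all treated.

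- Front-loaded: about 4–23% under the tolvaptan rules against 3–17% under the fluid-restriction rules. Examples: 6.5% v 3.6% (mean 4, SD 3, noise 1.0) and 16.7% v 12.1% (mean 5, SD 4, noise 1.0). The gap is roughly 1 to 6 points.
- Linear: the gap is essentially 0.

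**Step 3. Consequence for a test, as a function of extra early crossers.** Let p be the rate of > 10 mmol/L in 24 h, equal in both arms and always treated. Let q be the share who cross an early threshold but never exceed 10. For p I use 1.7%, 5.6% and 12.1%, the rates in the Background section (the first two are for > 12 mmol/L, so they are stand-ins). For q I assume 5–15%.

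If early crossers are treated only after tolvaptan, the rates are p + q and p. Chance of rejection = Φ[(q − 1.96·se₀)/se₁], where se₀ is the pooled and se₁ the unpooled standard error.

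Example: p = 0.056, q = 0.10, n = 83.
- se₀ = √(0.106 × 0.894 × 2/83) = 0.0478
- se₁ = √[(0.156 × 0.844 + 0.056 × 0.944)/83] = 0.0472
- Φ[(0.100 − 0.0937)/0.0472] = 0.55

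Over the grid, a two-sided 5% test rejects in about 15–92% of trials with no true difference. If clinicians also treat half of such cases under fluid restriction, the gap is 2.5–7.5 points and rejection about 6–30%.

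**Step 4. Precision for the arm-neutral event.** With equal rates p and 83 per arm, the 95% half-width is 1.96·√[2p(1 − p)/83]: 3.9, 7.0 and 9.9 points at 1.7%, 5.6% and 12.1%. With 12.1% v an assumed 2%, it is 1.96·√[(0.121 × 0.879 + 0.02 × 0.98)/83] = 7.6 points.

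**Step 5. What early dextrose does to that event.** In the front-loaded model (noise 1.0 on follow-up values only), suppose early dextrose fully stops the rise, an upper bound. The > 10 mmol/L rate is then about 1.8% on tolvaptan v 5.7% on fluid restriction (mean 5, SD 3), or 3.0% v 16.6% (mean 6, SD 4), with identical underlying courses.

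**The case against.** A reader might infer that re-lowering is triggered in the tolvaptan arm alone. The document does not support that. The overcorrection rule in {11b} covers every participant, and the statement there that dextrose is given for a faster-than-desired rise is not limited to one arm. The Abstract (Methods), {11a}, the Treatment questionnaire section and {18b} also speak of dextrose without limiting it to tolvaptan. Only the numerical early thresholds are tolvaptan-specific.

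A reader might also infer that the trial cannot test the safety hypothesis. That too is stronger than the text allows. Overcorrection is recorded as an SAE in both arms, and the first-24-h sodium increment is a listed secondary endpoint, so a first-day rate can be derived.

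Four further objections stand at least in part:

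- The gap is not inevitable. It needs a front-loaded rise and vanishes with a linear one.
- Sampling explains little: giving fluid restriction the same thresholds at 12-hourly sampling leaves only about 0–1.3 points in the same model.
- The bias probably runs against tolvaptan, so it makes false reassurance less likely.
- Replacing the outcome outright would create the opposite problem (Step 5), because rises aborted by early dextrose would disappear from view. Section {18b} openly takes a strategy view.

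The superiority design is a minor matter, since nothing in the article says that a non-significant difference will be read as safety. None of this makes the listed outcome a clean comparison of overcorrection, and the unlisted SAE rate does not fill the gap.

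**Conclusion.** The concern holds in a limited form. As defined, the main safety outcome combines how fast sodium rose with arm-specific rules for noticing and treating the rise, so it does not by itself answer the stated question about overcorrection. The event that would answer it is already defined in the protocol but is not an endpoint.

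The probable direction is an inflated tolvaptan rate. Its size cannot be fixed from the document: it rests on the shape of the rise, on measurement noise and on how often clinicians treat rises below 10 mmol/L under fluid restriction. The false-rejection figures in Step 3 are conditional on an assumed 5–15% of extra early crossers and are not forecasts.

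**What to change.** 1. List the proportion with a sodium rise above 10 mmol/L in 24 h as a main safety outcome, calculated identically in both arms from the daily early-morning samples that both already have.
2. Keep re-lowering therapy beside it, labelled as having numerical early triggers only after tolvaptan.
3. Interpret the two together, since early dextrose can prevent rises above 10 mmol/L and so lower the tolvaptan rate.
4. Report the risk difference with its 95% CI, and base any statement of no increase on the upper limit.
5. The investigators should reconcile the arm-neutral and tolvaptan-specific wording on dextrose in the Abstract (Methods), {11a}, {11b} with Table 2, and {18b}. No clinical threshold is proposed here.

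**Cost.** Changes to the outcome table and analysis wording, with no extra samples. The > 10 mmol/L outcome will have fewer events and a wide interval (Step 4). Rises visible only between daily samples will be missed. The comparison remains one of strategies with unequal safeguards, and the report should say so.

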### Participant timeline {13}

The participant timeline is shown in Table 4.

**Table 4 Tab4:**
[figure not shown]
Participant timeline

*Need for subsequent tolvaptan doses on days 2 and 3 reassessed daily according to protocol (based on serum sodium increment)

**Usual care may include fluid restriction or tolvaptan (patients administered tolvaptan prior to enrolment will not be included)

### Sample size {14}

The SALT 1 trial reported a mean difference between tolvaptan and placebo groups in sodium increment at day 4, of approximately 4 mmol/L. The standard deviation (SD) in day 4 sodium concentrations was approximately 4.9 (effect size 0.8). We determined that 2 mmol/L is the minimally clinically relevant difference between tolvaptan and fluid restriction. Using the same SD, we estimated that 64 participants per group would be required to detect this difference based on a *t*-test with 80% power and a 2-sided *p*-value equal to 0.05. To allow for drop-outs including autocorrection of hyponatraemia without specific therapy, a total of 166 participants will be recruited (83 per group).

In case of unforeseen difficulty with recruitment, we have done further power estimates to determine the number of participants required to detect a 3 mmol/L and a 4 mmol/L between group difference, using the same power and significance levels (Table 5). Expected minimum recruitment is 52 participants, or 68 accounting for an additional 30% recruitment margin.

**Table 5 Tab5:** Power calculations

Difference between arms	Number per group	+ 30% to allow for drop-outs and autocorrection	Total sample size
2 mmol/L	64	83	166
3 mmol/L	43	56	112
4 mmol/L	26	34	68

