Tolvaptan is an oral vasopressin V2-receptor antagonist that blocks AVP action in the kidney, inducing a water diuresis to raise serum sodium concentration. The efficacy of tolvaptan versus placebo (without fluid restriction) was established in the SALT-1 and SALT-2 trials in patients with mild-to-moderate hyponatraemia (mean baseline serum sodium 129.0 (SD 4.1) mmol/L). The SALT trials did not enrol acutely hospitalised patients; rather, patients with chronic hyponatraemia were electively admitted for the purpose of trial initiation, and patients with serum sodium less than 120 mmol/L and neurological symptoms were excluded [11]. Tolvaptan was approved in the USA by the Food and Drug Administration in 2009 for treatment of clinically significant hypervolaemic or euvolaemic hyponatraemia, defined as serum sodium < 125 mmol/L, or hyponatraemia that is symptomatic and has resisted correction with fluid restriction [12, 13]. The sodium cut-off recommendation from the FDA approval is not clearly evidence-based and instead is based on expert opinion regarding which patients with hyponatraemia are likely to benefit from treatment in general [12].

Off-label experience with tolvaptan post-approval has identified benefits and risks. While the SALT trials reported excessively rapid correction of hyponatraemia (rise in sodium > 12 mmol in 24 h) in 1.7% of tolvaptan-treated patients (5.6% of an SIAD subgroup), observational studies of tolvaptan in moderate-to-profound hyponatraemia have shown highly variable rates of biochemical overcorrection in patients with initial serum Na < 125 mmol/L, ranging from 0 to 30% of cases [14–17]. An international hyponatraemia registry observed overcorrection of serum sodium in 12.1% of cases of tolvaptan use [9]. This experience has led some to recommend reduced initial dosing of tolvaptan (e.g. 7.5 mg) to improve its safety profile [18, 19]. At least one case of osmotic demyelination due to tolvaptan has been published, in a patient with decompensated cardiac failure in whom tolvaptan was inappropriately continued for several days despite a large initial rise in serum sodium [20, 21].

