## Statistical methods

### Statistical methods for primary and secondary outcomes {20a}

For descriptive data, we will report either mean ± SD or median [IQR] depending on the distribution of the data. Change in serum sodium from baseline (day 1 0600 hours) to day 4 0600 hours (or day of discharge if earlier) will be compared between treatment groups. We will also compare the change in average daily area under the curve (AUC) for the serum sodium concentration from baseline to day 4, in line with analysis performed in the SALT trials [11]. A mixed-effects model based on restricted maximum likelihood (REML) will be used to account for both within-subject variation over time and between-subject variation to assess the treatment effect, namely the mean adjusted difference (MAD) between the control and the tolvaptan group surrounded by a profiled 95% confidence interval. Analysis will be by the intention-to-treat principle (ITT) so that data from participants who withdraw or violate the protocol will be included in their assigned treatment group. We will also perform a per-protocol sensitivity analysis. Plans for the statistical analysis and reporting of each secondary outcome will be decided upon by investigators with access to pooled data.

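### The trial is sized on the SD of day-4 sodium levels while the primary endpoint is the change from day 1 to day 4, so the variance behind Table 5 is unsupported unless the analysis is baseline-adjusted

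*Protocol article*

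**What the plan says.** All references are to the protocol article.

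- **Outcomes {12}, Table 3** gives the primary endpoint as "Change in serum sodium concentrations over time, from day 1 to day 4".
- **Statistical methods {20a}** says: "Change in serum sodium from baseline (day 1 0600 hours) to day 4 0600 hours (or day of discharge if earlier) will be compared" between the arms. It then specifies the model: "A mixed-effects model based on restricted maximum likelihood (REML) will be used to account for both within-subject variation over time and between-subject variation". The treatment effect is reported as a mean adjusted difference, but the section does not say what it is adjusted for.
- **Sample size {14}** starts from a cited placebo-controlled trial, with a "mean difference between tolvaptan and placebo groups in sodium increment at day 4, of approximately 4 mmol/L", and continues: "The standard deviation (SD) in day 4 sodium concentrations was approximately 4.9 (effect size 0.8"). It sets the target: "We determined that 2 mmol/L is the minimally clinically relevant difference between tolvaptan and fluid restriction". The same SD is carried into a two-sided t-test at the 5% level with 80% power. Table 5 lists 64, 43 and 26 per group for differences of 2, 3 and 4 mmol/L.
- **Background {6a}** gives the only baseline SD in the article, for the two cited placebo-controlled trials: "mean baseline serum sodium 129.0 (SD 4.1) mmol/L".

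The article states no SD of the day 1 to day 4 change and no correlation between the two days.

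**The concern.** The effect size of 0.8 has a difference in increments as its numerator and the spread of a level as its denominator (4 / 4.9 = 0.82). A t-test on change needs the SD of change, which depends on the baseline SD, the day-4 SD and the correlation between them. It can lie well above or well below the day-4 SD.

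This affects the fallback rows as well as the headline row. The section names 52 participants, which is 26 per group, as its expected minimum recruitment, so the 4 mmol/L row may be the one that matters in practice. If the analysis is an unadjusted comparison of change, the 80% attached to these sizes has not been shown to be the power of the planned comparison.

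**Working it through.** **Inputs.** Day-4 SD 4.9, differences of 2, 3 and 4 mmol/L, 64, 43 and 26 per group, two-sided 5% level and 80% power come from Sample size {14}. The baseline SD of 4.1 comes from Background {6a}; applying it to this trial is an assumption. The correlation r is not in the article and is assumed to lie between 0.2 and 0.7. All powers are for a two-sample t-test (noncentral t).

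**Step 1: reproduce Table 5 at SD 4.9.**

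- 3 mmol/L: 42.9, so 43 per group. This matches, with 80% power.
- 4 mmol/L: 24.6, so 25 per group; with the effect size rounded to 0.8 it is 25.5, so 26. This matches; 26 per group gives 82%.
- 2 mmol/L: 95.2, so 96 per group. The printed 64 does not follow. At 64 per group the power is 63%. A figure of 64 corresponds to an effect size of 0.5 (63.8), that is, an SD of about 4.0.

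**Step 2: SD of change.**

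SD of change = sqrt(4.1² + 4.9² − 2 × r × 4.1 × 4.9) = sqrt(40.82 − 40.18 r)

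Setting this equal to 4.9 gives r = 4.1 / (2 × 4.9) = 0.42. Only near that value does the day-4 SD stand in correctly for the SD of change.

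**Step 3: power of an unadjusted comparison of change at the printed sizes.**

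| r | SD of change | 3 mmol/L, 43 per group | 4 mmol/L, 26 per group | 2 mmol/L, 64 per group |
|---|---|---|---|---|
| 0.2 | 5.73 | 67% | 70% | 50% |
| 0.3 | 5.36 | 73% | 75% | 55% |
| 0.5 | 4.55 | 86% | 87% | 69% |
| 0.7 | 3.56 | 97% | 98% | 88% |

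The last column starts from 63% at SD 4.9, so most of its shortfall from 80% at low r is the separate error found in step 1. In sample-size terms, 80% power for 3 mmol/L needs 59 per group at r = 0.2 and 24 at r = 0.7, against 43 printed. For 4 mmol/L it needs 34 and 14, against 26 printed.

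**Step 4: power if day-4 sodium is adjusted for baseline.**

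Residual SD = 4.9 × sqrt(1 − r²), which never exceeds 4.9.

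| r | Residual SD | 3 mmol/L, 43 per group | 4 mmol/L, 26 per group | 2 mmol/L, 64 per group |
|---|---|---|---|---|
| 0 | 4.90 | 80% | 82% | 63% |
| 0.2 | 4.80 | 82% | 84% | 65% |
| 0.3 | 4.67 | 84% | 86% | 67% |
| 0.5 | 4.24 | 90% | 92% | 75% |
| 0.7 | 3.50 | 98% | 98% | 89% |

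Under this analysis the 3 and 4 mmol/L rows do not fall below plan at any r. The 2 mmol/L row still misses 80% at r = 0.5.

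**The case against.** The case for leaving the section alone has several parts.

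- **The target differences are not in question.** Under randomisation the expected difference between arms in day-4 level equals the expected difference in change. A reader might infer that every figure in Table 5 belongs to a different statistic from the one compared. That is too strong: only the variance can differ, and the 64 does not come from SD 4.9 in the first place.
- **The direction is unknown.** A reader might also infer that the trial is underpowered because of this mismatch. The article does not show that. The assumed range of r straddles the point where the mismatch vanishes, and above it 4.9 is conservative.
- **The planned model may already adjust for baseline.** Sizing a baseline-adjusted analysis on the SD of the outcome level is ordinary conservative practice, and the article speaks of an adjusted difference. The covariate list may sit in an analysis plan that is not shown.
- **The baseline SD is borrowed.** The 4.1 describes the two cited trials together, in mild-to-moderate hyponatraemia, while this trial enrols sodium of 115–130 mmol/L. The break-even r moves with it: 0.36 at a baseline SD of 3.5 and 0.50 at 4.9.
- **The 4.9 may simply be mislabelled.** It could be the SD of the increment described in the preceding sentence. Only the cited report can settle that.

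The first two parts stand and limit the point to the variance, with no claim of direction. The third is a good answer only if baseline is in fact a covariate; the methods section describes a comparison of change and does not say so, and the sample size section does not give this rationale. The fourth affects the exact powers but not the absence of a supported SD. The fifth, if true, is itself a reason to correct the label and cite the source.

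**Conclusion.** The point holds as a statement about variance. The protocol article labels its SD as that of day-4 concentrations and uses it to size a comparison of change, without giving an SD of change or a correlation. For an unadjusted comparison of change, with a baseline SD of 4.1 and r from 0.2 to 0.7 (both assumptions), power runs from 67% to 97% in the 3 mmol/L row and from 70% to 98% in the 4 mmol/L row. The printed sizes agree with SD 4.9 only near r = 0.42.

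This does not show that the trial is too small. With baseline adjustment, and if the day-4 SD here is about 4.9 as in the cited trial, the 43 and 26 per group rows keep at least about 80% and 82%.

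The 2 mmol/L row is a distinct error that needs no assumption about r: the stated inputs require 96 per group, not 64, and 64 gives about 63% power.

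**What to change.** **Preferred.** State in Statistical methods {20a} that the primary comparison is day-4 sodium adjusted for baseline sodium, with baseline as a covariate in the mixed model. Add to Sample size {14} that 4.9 is then an upper bound on the residual SD, which equals 4.9 × sqrt(1 − r²), so that 43 and 26 per group give at least about 80% and 82% for 3 and 4 mmol/L. Baseline sodium is already collected, so this costs a few words and removes the dependence on an unknown SD of change.

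**Otherwise.** If an unadjusted comparison of change is kept, recompute all three rows of Table 5 with an SD of the day 1 to day 4 change, taken from the source of the 4 mmol/L figure or from pooled blinded trial data, and cite it. This costs one recalculation, and the stated power may turn out less favourable.

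**In either case.** Correct the 2 mmol/L row: at SD 4.9, report about 63% power at 64 per group, or 96 per group for 80%. With the article's own 30% margin, 96 × 1.3 gives 125 per group, or 250 in total, against 166 printed.

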### Trial design {8}

We will conduct a 3-day, parallel group, open-label, randomised, controlled trial of tolvaptan versus fluid restriction in hospitalised patients with moderate-to-profound hyponatraemia (Na 115–130 mmol/L). Patients will be randomised 1:1 to the tolvaptan or fluid restriction groups, with the intervention titrated daily based on serum sodium response according to a pre-determined protocol. The trial is designed to determine superiority. A 24–48h run-in period prior to randomisation will allow exclusion of patients with autocorrection of hyponatraemia due to an acutely reversible cause of non-osmotic AVP release.

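### The 30% sample-size margin counts autocorrection as drop-out, but the intention-to-treat analysis keeps autocorrectors, so they dilute the difference and the margin holds 80% power only at low autocorrection rates

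*Protocol article*

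**What the plan says.** The Sample size section {14} of the protocol article bases its calculation on a "t*-test with 80% power and a 2-sided *p*-value equal to 0.05". The target difference is given as follows: "We determined that 2 mmol/L is the minimally clinically relevant difference between tolvaptan and fluid restriction". The SD comes from an earlier placebo-controlled trial: "The standard deviation (SD) in day 4 sodium concentrations was approximately 4.9 (effect size 0.8"). The section continues: "Using the same SD, we estimated that 64 participants per group would be required". It then adds the margin: "To allow for drop-outs including autocorrection of hyponatraemia without specific therapy, a total of 166 participants will be recruited (83 per group"). Table 5 applies the same 30% addition, for drop-outs and autocorrection together, to all three rows: 64 to 83, 43 to 56, and 26 to 34 per group.

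Statistical methods {20a} sets an intention-to-treat analysis in which "data from participants who withdraw or violate the protocol will be included in their assigned treatment group". Under Intervention description {11a} and Table 1, a participant in either arm whose sodium normalises moves to a 1500 mL restriction, or to no intervention if the preceding 24 h rise exceeded 8 mmol/L. Neither rule takes the participant out of the trial.

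On screening, Trial design {8} says that a "run-in period prior to randomisation will allow exclusion of patients with autocorrection of hyponatraemia" due to an acutely reversible cause. The only criterion in Eligibility criteria {10} based on a sodium rise excludes rises above 0.5 mmol/L/h or above 10 mmol/L/24 h. Sodium must also lie between 115 and 130 mmol/L.

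**The concern.** A head-count margin replaces participants who supply no outcome. A randomised autocorrector does supply one: the day 4 sodium is measured and analysed in the assigned arm. If sodium would have recovered anyway, that participant adds little or nothing to the contrast between arms. The cost is a smaller expected difference, and required n grows with the inverse square of the difference. A margin sized for loss therefore buys less protection against autocorrection than it appears to.

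At stake is whether 166, or the fallbacks of 112 and 68, carry the stated 80% power under the plan's own analysis. The wording also leaves room to treat autocorrectors as drop-outs later, which would break the intention-to-treat comparison.

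**Working it through.** **Inputs.** From the Sample size section: differences of 2, 3 and 4 mmol/L; SD 4.9; two-sided 0.05; 80% power; t-test; base n of 64, 43 and 26 per group; margin 30%. From Trial design, equal allocation: "Patients will be randomised 1:1 to the tolvaptan or fluid restriction groups". The article gives no autocorrection rate p, so 10, 20 and 30% are assumed to show a range.

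**1. The plan's own figures.**
- The margin reproduces as multiplication: 64 × 1.3 = 83.2, 43 × 1.3 = 55.9, 26 × 1.3 = 33.8, giving 83, 56 and 34.
- The 3 mmol/L row reproduces at SD 4.9: 42.9, rounded up to 43.
- The 4 mmol/L row gives 24.6 (25) at SD 4.9, or 25.5 (26) at the rounded effect size of 0.8.
- The 2 mmol/L row does not reproduce. At SD 4.9 the standardised difference is 2/4.9 = 0.408 and the t-test needs 95.2, so 96 per group. The stated 64 corresponds to a standardised difference of 0.5, that is, SD 4.0.

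Below, the 2 mmol/L row uses SD 4.0, so that this base error is not charged to autocorrection. The other rows use SD 4.9.

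**2. What the margin covers as pure loss.** 1 − 64/83 = 22.9%; 1 − 43/56 = 23.2%; 1 − 26/34 = 23.5%.

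**3. What it covers as dilution.** If a proportion p in both arms has no treatment effect and the SD is unchanged, the expected difference is δ(1−p) and required n is multiplied by 1/(1−p)². That factor is 1.23, 1.56 and 2.04 at 10, 20 and 30%. For 2 mmol/L at SD 4.0 the t-test then needs 79, 100 and 130 per group.

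T-test power with every randomised participant analysed:

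| Row | n per group | SD | p = 0 | 10% | 20% | 30% | 80% power held up to |
|---|---|---|---|---|---|---|---|
| 2 mmol/L | 83 | 4.0 | 89% | 82% | 73% | 61% | 12.5% |
| 3 mmol/L | 56 | 4.9 | 89% | 82% | 73% | 61% | 12.8% |
| 4 mmol/L | 34 | 4.9 | 91% | 85% | 76% | 64% | 15.5% |

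The last row has slightly more room because its base of 26 exceeds the 25 that SD 4.9 needs. From the margin alone, the break-even is 1 − √(1/1.3) = 12.3%.

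**4. Using the whole margin as dilution.** If the roughly 23% that the margin can absorb as loss were all retained autocorrectors, power would be 69, 69 and 72% in the three rows.

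**5. Both at once.** For 2 mmol/L at SD 4.0, 10% true loss leaves 83 × 0.9 = 74.7 per group. With 10% autocorrection as well, power is 78%; with 20%, 68%.

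**6. The separate base error.** At SD 4.9, 83 per group has 74% power for 2 mmol/L with no loss and no autocorrection.

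**7. Screening.** A patient whose sodium rises unaided more slowly than the rapid-rise limits, and who is still at or below 130 mmol/L, meets the listed criteria and can be randomised. The run-in statement is broader than the criteria that would put it into effect.

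**The case against.** The best defence is that the margin may be enough. The dilution model is the extreme case, with zero treatment effect in every autocorrector, and at 10% autocorrection all three rows still exceed 80% (the first only at SD 4.0). That stands: failure depends on a rate the article does not give, so a flat statement that the three targets miss 80% because of autocorrection is not supported.

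The 2 mmol/L could also be read as the intention-to-treat contrast itself, already half the 4 mmol/L seen against placebo. On that reading no dilution applies, but autocorrection then needs no margin either. Counting it as drop-out is wrong both ways.

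The margin might instead be meant for patients removed during the run-in, before randomisation. The per-group figure speaks against this, as do allocation at consent (Implementation {16c}) and the Discussion's statement that recruitment itself is delayed by at least 24–48 h.

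Three stronger inferences are tempting and fail:
- A reader might infer that eligibility admits most autocorrectors. No share is given, and the run-in, the 130 mmol/L ceiling and the rapid-rise exclusion each remove some. The Discussion claims only to mitigate the problem.
- A reader might call it an error that 83 covers 23% loss and not 30%. The article describes an added 30% margin and never states an expected 30% loss.
- A reader might quote the powers at SD 4.9 for the 2 mmol/L row (65, 55 and 45% at 10, 20 and 30%) as the harm from autocorrection. Much of that shortfall is the base error, since power starts at 74% with none.

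Covariate choice can fairly be left to an analysis plan, so that part of the fix is a recommendation and not the correction of an error.

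**Conclusion.** The point holds in limited form. The Sample size section and Table 5 treat autocorrection as a loss of participants, while the analysis rule and the handling of normalised participants make it a loss of effect. Assuming no treatment effect in autocorrectors, equal rates in both arms, unchanged SD and no true loss, the margin holds 80% power up to about 12.5% autocorrection (13% and 15.5% in the fallback rows). At 20% autocorrection, power falls to 73–76%, and at 30% to 61–64%. The 2 mmol/L figures depend on SD 4.0; at the SD the article states, 74% is the ceiling for 83 per group, for a different reason. The run-in statement and the eligibility criteria do not match and must be reconciled. This deserves correction but does not invalidate the design.

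**What to change.** In the Sample size section, replace the joint margin with two stated assumptions: a rate of missing day 4 sodium (83 down to 64 covers 23%), and a rate of retained autocorrection, expressed as a smaller expected intention-to-treat difference. Restate the power of 166, 112 and 68 over a range of both, after settling whether the 2 mmol/L row rests on SD 4.0 or 4.9. State that randomised autocorrectors stay in the intention-to-treat analysis. Include the pre-randomisation sodium increment, already needed for eligibility, as a baseline covariate in the mixed model. Reconcile the run-in statement in Trial design with the criteria in Eligibility criteria.

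This adds no patients. The cost is a less favourable stated power and one more covariate.
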